### Other data collection

Clinical outcomes: age at diagnosis (prenatal, postnatal), genetic anomaly, NYHA functional class, blood pressure, body mass index (BMI), healthcare usage (primary and secondary care contacts, hospitalisation), pacemaker, implantable cardioverter defibrillator (ICD), cardiac surgery, and medication.Socio-economic status of the patient’s family.Safety outcomes.

### Sample size

We aim to recruit a total of 214 children in both groups. The primary outcome is the difference in the self-reported QoL score with the PedsQL instrument between the children with inherited cardiac disorders and the control group. We used the results from our previous QoL cross-sectional studies in patients with CHD to calculate the sample size [4, 21, 26–29, 39]. In our experience, as well as in similar studies using patient related outcomes, a difference of less than 5 points is not clinically relevant, and a difference of more than 10 points is ideal, but rarely achieved [2, 27, 29]. Therefore, we hypothesized to observe a difference in the total QoL score of 7 ± 15 points (over 100). With a 90% power, a bilateral alpha risk of 5%, and potentially 10% of loss to follow-up or missing data on the primary outcome, we need to include 107 patients in the group 1 and 107 patients in the group 2.

### Statistical analysis

Patients’ characteristics will be presented using mean and standard deviation for continuous variables, and frequencies and proportions for categorical variables. QoL scores will be calculated with the parametric Student’s t test when the distribution was Gaussian and with the Mann–Whitney test otherwise. The effect size will be estimated using Cohen’s d measure.

Association between QoL scores and physical activity, clinical and socio-demographic data will be studied using Pearson’s or Spearman’s coefficient. According to the type of relation between QoL scores and these factors, a multiple linear regression or a generalized additive model (GAM) will be implemented for the different scores. In the GAM, a parametric portion of the model could be identified (with the vector of parameters associated with the set of explanatory variables). The non-parametric part of the model could be formed by smooth functions for clinical characteristics or age effects for example. One of the main advantages of the GAM implemented is the possibility to address the issue of linear dependency (i.e. collinearity) between these characteristics or age effects which often impedes their simultaneous estimation.

When considering multiple comparisons, the type I error will be adjusted.

The statistical significance will be set at 0.05 and analyses will be performed using Statistical Analysis Systems version 9 (SAS Institute, Cary, NC, USA). Data will be managed by the clinical research unit of Montpellier University Hospital, France, in collaboration with the paediatric and congenital cardiology department.

### Ethics

The study will be conducted in compliance with the Good Clinical Practices protocol and Declaration of Helsinki principles. It was approved by a drawn national Ethics Committee (CPP Sud-Est VI, 2020-A00411-38). Informed consent will be obtained from all parents or legal guardians, and oral assent will be obtained from all children. The study was registered on Clinicaltrials.gov (NCT04712136).

## Expected results and perspectives

In the continuity of our research program on QoL and physical activity in paediatric and congenital cardiology [4, 21, 22, 26, 26–29, 39], the QUALIMYOTYRHM trial should provide, for the first time, reliable data on health-related quality of life and physical activity in children with inherited cardiac arrhythmia or inherited cardiomyopathy. From our perspective, considering the QoL as the main outcome of this trial is both original and primordial in this young population with cardiac inherited disorders. Indeed, measuring patient-reported outcomes (PRO) in paediatric cardiology should become a priority, considering that many young cardiac patients experience a low level of physical impairment during childhood, but an increased cardio-vascular risk during adulthood [2, 3, 40]. This is also in line with the European Medicines Agency (EMA) promotion of PRO measures in clinical research, and more and more drug trials, even in paediatrics, currently evaluate the quality of life as a secondary outcome [41]. Moreover, our results will contribute to provide consistent baseline clinical and QoL data for future interventional clinical trials in children with inherited cardiac arrhythmia or inherited cardiomyopathy.

The QUALIMYORYTHM trial also seeks to determine the level of physical activity in the contemporary generation of children with inherited cardiac disorders, using modern connected technology adapted to this population, such as fitness trackers. In the absence of any reliable risk stratification in those children, the current guidelines on eligibility of young athletes with inherited cardiac disorders for sports participation mainly rely on expert opinions [42–45], and conclusions by the experts have classically not been the same on both sides of the Atlantic [46]. The difference commonly made between recreational and competitive sport is probably more about medico-legal issues for the practitioner, than for the patient's own interest. For example, more than a decade ago, the European guidelines for competitive sport participation in the long QT syndrome were very restrictive [43]. Yet, in a recent study from a cohort of 172 appropriately managed children with long QT syndrome, cardiac event rates were low and occurred during recreational, but not competitive activities [47]. Similarly, in a cohort of 129 young athletes with ICD, most of them having a long QT syndrome or a hypertrophic cardiomyopathy, and participating in competitive or dangerous sports, there were no occurrences of death, arrest, or injury related to arrhythmia, during sports; interestingly, this study found that 27% patients received at least one shock, only 4 during sports, which is similar to unselected non-athletic paediatric ICD cohorts [48]. Based on convergent studies reporting a low risk of cardiac event in athletes with optimal treatment for long QT syndrome [47–50], a progressive trend towards a different medical approach has been observed, involving the patient-athlete in shared decision-making. Therefore, the 2015 US guidelines [51] have been less restrictive regarding high intensity recreational exercise and competitive sports, especially for asymptomatic genotype-positive/phenotype-negative athletes. More recently, the 2020 European guidelines have moved one step further in promoting supervised and regular physical activity in patients with inherited cardiac disorders [45].

Nevertheless, most published studies are retrospective and have not evaluated sports with the highest cardiovascular demand (only a few class IIIB and IIIC sports), or recreational sports in children with the rarest or most serious inherited cardiac disorders. Indeed, in their recent review, Masrur et al. concluded that there are insufficient data on the risks of exercise in Brugada syndrome to make recommendations for exercise [52]. Therefore, the QUALIMYORYTHM trial should contribute to precise how the recommendations are currently applied “in the real life”, and measure their potential impact on QoL and physical activity in children with inherited cardiac arrhythmia or inherited cardiomyopathy.

Furthermore, the QUALIMYORYTHM trial will provide, for the first time in a population of children with inherited cardiac disorders, consistent cardiopulmonary fitness data, such as the maximum oxygen uptake (VO2_max_), the anaerobic threshold, the ventilatory efficiency, and the exercise stroke volume. Moreover, this study will also bring original information about the level of motivation of children with inherited cardiac disorders for physical activity, and its degree of correlation with the actual levels of physical activity and exercise capacity. In paediatric cardiology, cardiopulmonary fitness has mainly been determined in children with CHD [5, 53], but these results cannot be easily transposed to inherited cardiac disorders, as the underlying pathophysiology and haemodynamic consequences are different. For instance, animal models have demonstrated that the beneficial effects of training on the heart effects of training are related to the signalling pathways of myocardial hypertrophy and fibrosis, but such findings need to be further analysed in patients with inherited cardiomyopathy [54].

If the QUALIMYORYTHM trial finds that physical activity and exercise capacity in children with inherited cardiac arrhythmia or inherited cardiomyopathy are similar to those of healthy children, without any additional risk, the level of evidence for future guidelines on sports eligibility in this population will be significantly improved. Conversely, if physical activity and exercise capacity in children with inherited cardiac disorders are significantly impaired, it will open a new research field on rehabilitation programs in this population. Indeed, if physical deconditioning is diagnosed and managed at an early stage in patients with inherited cardiac disorders, participation in rehabilitation programs could reverse the vicious circle of deconditioning, and, ultimately participate in reducing the cardio-vascular risks related to inactivity, as it has been suggested in CHD [22, 55–57], as well as in many chronic diseases [58].

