## Background

Prognosis of children with congenital cardiac disorders has significantly improved in the past two decades, due to great advances in prenatal screening, intensive neonatal care and modern invasive therapies [1]. As a result, more attention has been recently given to health-related quality of life (QoL) and secondary prevention in paediatric cardiology [2, 3].

Traditionally, congenital cardiac disorders are divided into 3 groups: congenital heart disease (CHD) for structural cardiac anomalies, inherited cardiac arrhythmia and inherited cardiomyopathy. So far, QoL studies in paediatric cardiology have mainly focused on the group of children with CHD and, although the overall level of QoL is good in this population, our group highlighted the existing correlation between exercise capacity and QoL, and the risk for physical deconditioning, even for non-serious CHD [4, 5]. Indeed, despite the promotion of physical activity in the current guidelines [6–8], many children with CHD experience social barriers to physical activity and “remain on the side-line” at school or in their social life [9]. Ultimately, these patients may be exposed to the consequences of a sedentary lifestyle: overweight, high blood pressure, social exclusion, and impaired QoL [10–12]. Conversely, patients with CHD who have been physically active since childhood are less likely to become sedentary adults [13].

Such consistent data are not available in the literature for children from the two other groups, e.g. inherited cardiac arrhythmia or inherited cardiomyopathy, for which QoL and physical activity have been rarely studied. Some heterogeneous data were provided from small paediatric [14–16] or adult [17, 18] cohorts, however no prospective controlled study has analysed the determinants of QoL and the level of physical activity in children with inherited cardiac disorders [19]. We hypothesized that QoL scores and physical activity levels in children with inherited cardiac disorders are reduced compared to the healthy subjects.

Therefore, the multicentre observational controlled QUALIMYORYTHM trial aims to evaluate the QoL, exercise capacity, and the level of physical activity of children with inherited cardiac arrhythmia or inherited cardiomyopathy, in comparison with a matched control population. This study will also evaluate the main factors associated with QoL in this population.

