### Study design

The QUALIMYORYTHM trial is a prospective, multicentre controlled observational study with a follow-up of 2 weeks and a recruitment duration of 18 months. All screened subjects will be identifiable throughout the study by a unique subject number. The eligible patients will be divided into 2 groups (Fig. 1):

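### Two weeks of follow-up cannot support a conclusion of no additional risk, and a non-significant difference in activity or exercise capacity would not by itself show similarity

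*Protocol article*

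**What the plan says.** The Expected results and perspectives section describes two outcomes. In the first, activity and exercise capacity "are similar to those of healthy children, without any additional risk, the level of evidence for future guidelines on sports eligibility in this population" would be significantly improved. The second, introduced as the converse, is the case "if physical activity and exercise capacity in children with inherited cardiac disorders are significantly impaired"; that would open research on rehabilitation.

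Elsewhere in the protocol article:

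- **Background.** The hypothesis is that "QoL scores and physical activity levels in children with inherited cardiac disorders are reduced compared to the healthy subjects". The aim covers quality of life, exercise capacity and physical activity "in comparison with a matched control population".
- **Objectives.** Only quality of life is compared between groups. Activity and exercise capacity appear as factors against which quality of life is assessed.
- **Study design.** The study is prospective, "with a follow-up of 2 weeks and a recruitment duration of 18 months".
- **Sample size.** The calculation rests on the PedsQL total score alone: "we hypothesized to observe a difference in the total QoL score of 7 ± 15 points (over 100"; hence "we need to include 107 patients in the group 1 and 107 patients in the group 2".
- **Statistical analysis.** Student's t or Mann-Whitney is named for quality-of-life scores, with Cohen's d, at the 0.05 level. Correlation, regression and additive models address factors associated with quality of life.
- **Other data collection.** Safety outcomes are listed without further detail.
- **Table 1.** Children with absolute contraindications to exercise testing are excluded, including uncontrolled symptomatic arrhythmia and uncontrolled heart failure.

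**The concern.** Two separate inferences are joined in one sentence.

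The first concerns risk. Absence of added risk is a statement about uncommon events. It needs enough person-time, a defined event and a population that includes the children in whom events are expected. The article describes two weeks per child, no event definition, and exclusion of the least stable children.

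The second concerns similarity. Because *similar* is set against *significantly impaired*, the natural reading is that it means not significantly different. A test of difference that fails to reject does not show that the difference is small.

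At stake is what the trial may claim about sports eligibility. The abstract's Discussion gives better evidence for such guidelines as a purpose of the trial, so an uninformative result could be cited as a reassuring one.

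**Working it through.** **The plan's own figure.** Difference 7, SD 15, two-sided 5%, power 90%:

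n per group = 2 × (1.960 + 1.282)² × (15/7)² = 96.5, rounded up to 97.

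Allowing for 10% loss: 97 × 1.10 = 106.7 → 107, or 97 / 0.90 = 107.8 → 108. The stated 107 reproduces. For the secondary outcomes I use 107 × 0.90 ≈ 96 evaluable per group, which assumes the same loss.

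**Risk.** Inputs: 107 patients and 14 days (Sample size, Study design).

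- Person-time in the patient group: 107 × 14 / 365.25 = 4.10 patient-years (8.2 for both groups together).
- Zero events, one-sided 95% upper limit: −ln(0.05) / 4.10 = 0.73 per patient-year. The upper end of the two-sided 95% interval is −ln(0.025) / 4.10 = 0.90.
- Per child over two weeks: 1 − 0.05^(1/107) = 2.8%.

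The article gives no event rate, so a range is assumed:

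| Assumed true rate per year | Expected events in 4.10 patient-years | Chance of seeing none |
|---|---|---|
| 1% | 0.04 | 96% |
| 2% | 0.08 | 92% |
| 5% | 0.21 | 81% |

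Across this range, no events is by far the likeliest result, so observing none would hardly distinguish these rates.

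**Similarity, in SD units.** The 95% CI half-width is 1.96 × √(2/n): 0.28 SD with 96 per group and 0.27 SD with 107. The chance that a true deficit is non-significant:

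| True deficit | 96 per group | 107 per group |
|---|---|---|
| 0.2 SD | 72% | 69% |
| 0.3 SD | 45% | 41% |
| 0.4 SD | 21% | 17% |

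Number per group for 90% power to show equivalence when the true difference is zero, 2 × ((z_crit + 1.645) / margin)², with the margin in SD units. The margins are assumed because the article gives none:

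| Margin | 90% CI inside margin (z_crit 1.645) | 95% CI inside margin (z_crit 1.960) |
|---|---|---|
| 0.2 SD | 542 | 650 |
| 0.3 SD | 241 | 289 |
| 0.4 SD | 136 | 163 |
| 0.5 SD | 87 | 104 |

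**The same in points of % predicted VO2max.** SDs of 15 to 20 are assumed, with 96 per group. SE = SD × √(2/96) = 2.17 to 2.89.

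- CI half-width 1.973 × SE = 4.3 to 5.7 points. An observed deficit just under this is non-significant, while its interval reaches twice as far, 8.5 to 11.4 points.
- Equivalence power at a true difference of zero, 2Φ(margin/SE − t) − 1, with assumed margins. With t = 1.653 (90% CI): 49% for 5 points at SD 15, 6% for 5 points at SD 20, 93% for 10 points at SD 20. With t = 1.973 (95% CI): 26%, 0% and 86%. The 0% arises because the 5.7-point half-width already exceeds the 5-point margin.

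**The case against.** The sentence is conditional and sits in a perspectives section. It says evidence would improve if similarity without added risk were found; it does not say that p > 0.05 will be read as similarity. A reader might infer a decision rule, but the article contains none. That reading comes from the contrast with significant impairment and from the named tests. This objection stands and limits the weight of the point.

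A reader might also count the missing margin, or the lack of named tests for activity and exercise testing, as omissions. An article may leave these to the full protocol or analysis plan, neither of which is shown, so they are not faulted here. Cohen's d is also planned. It estimates size, but without a margin it cannot establish similarity.

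A third tempting reading is that the sample is too small to show equivalence. The figures do not support that in general: a 0.5 SD margin is roughly within reach, while 0.2 or 0.3 SD is not. The SDs and margins are assumptions, and none is offered for MET.

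Nor does the text say that sports restrictions would be relaxed. It speaks only of the level of evidence.

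Finally, hospitalisation, healthcare usage and defibrillator status are also collected, with no time window stated. The 0.73 limit therefore applies only to events in the two-week follow-up. These extra data do not rescue the risk clause, because the article does not tie them to sport exposure or to a defined event.

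**Conclusion.** The point holds in two parts of unequal strength.

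The risk part is firm. About 4.1 patient-years, in a sample that excludes the least stable children and with no event specified in the article, cannot show absence of additional risk. Zero events would be compatible with up to 0.73 per patient-year. No analysis plan could change this, since it follows from the length of follow-up. It assumes that risk is judged from the prospective two weeks.

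The similarity part is a caution. A non-significant comparison with an interval of ±0.28 SD does not by itself establish similarity; the size of the shortfall depends on a margin not given in the article.

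There is also a mismatch within the document: the Background aims at a group comparison of activity and exercise capacity that the Objectives do not list, and the perspective sentence depends on it.

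The primary outcome, its sample size and its test are unaffected. The change is worth making because it alters what the trial can claim.

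**What to change.** 1. In Expected results and perspectives, delete absence of additional risk as a possible conclusion. Report any events descriptively, as counts and person-time with an exact upper confidence limit.
2. In Objectives, add the between-group comparison of MET and % predicted VO2max as a secondary objective, matching the Background aim. Report each as a difference with a 95% CI from a pre-specified comparison.
3. Use the word similar only if that interval lies wholly inside a margin fixed and justified before the data are seen. If the interval neither fits inside the margin nor shows a difference, call the result inconclusive.

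The cost is wording only: no extra patients, visits or measurements. The downside is a more modest claim, and with a narrow margin an inconclusive result is likely at this sample size.

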### Study limitations

The subjects in the control group will be recruited at the hospital and may not be considered as healthy as if they were recruited from the general population. However, this bias was limited in our previous similar studies, which showed very good correlations between QoL scores and VO2_max_ values with the respective normal values reported in the literature among the general population [5, 39].

## Data Availability

Not applicable.

## Abbreviations

CHD: Congenital heart disease
CPET: Cardiopulmonary exercise test
QoL: Health-related quality of life
